### 10.4 ASSESSMENT OF AES AND SAES

Seriousness, causality, severity and expectedness will be assessed by the Principal Investigator or another suitably qualified physician in the research team. Cases that are considered serious, possibly, probably or definitely related to either IMP and unexpected (i.e. SUSARs) will be thoroughly investigated.

The Investigator is responsible for assessing each AE. This may be delegated to other suitably qualified physicians in the research team who are trained in recording AEs and recording and reporting SAEs.

The Chief Investigator (CI) may not downgrade an event that has been assessed by an Investigator as an SAE or SUSAR, but can upgrade an AE to an SAE, SAR or SUSAR if appropriate.

#### 10.4.1 Assessment of Seriousness

The Investigator will make an assessment of seriousness as defined in Section 10.1.

#### 10.4.2 Assessment of Causality

The Investigator will make an assessment of whether the AE/SAE is likely to be related to the IMP according to the definitions below.

- Unrelated: where an event is not considered to be related to the IMP.
- Possibly Related: The nature of the event, the underlying medical condition, concomitant medication or temporal relationship make it possible that the AE has a causal relationship to the study drug. The assessment of causality will be made against the reference safety information found in the Section 4.8 of the relevant Summary of Product Characteristics.

The reference safety information i.e. known undesirable effects are detailed in the SmPC Reference Document which is stored in the site file and pharmacy file (see also Section 6.1.8).

Where there are concomitant medications, if the AE is considered to be related to an interaction between the IMP and the other medication, or where the AE might be linked to either the IMP or the other medication but cannot be clearly attributed to either one of these, the event will be

considered as an AR. Alternative causes such as nature of the HMB, other risk factors and the temporal relationship of the event to the treatment should be considered and investigated.

#### 10.4.3 Assessment of Expectedness

If an event is judged to be an AR, the evaluation of expectedness will be made based on knowledge of the reaction and the relevant product information documented in the SmPC which is stored in the site file and pharmacy file.

The event may be classed as either:

**Expected:** the AR is consistent with the toxicity of the IMP listed in the SmPC.

**Unexpected:** the AR is not consistent with the toxicity in the SmPC.

#### 10.4.4 Assessment of Severity

The Investigator will make an assessment of severity for each AE/SAE and record this on the SAE form according to one of the following categories:

**Mild:** an event that is easily tolerated by the participant, causing minimal discomfort and not interfering with every day activities.

**Moderate:** an event that is sufficiently discomforting to interfere with normal everyday activities.

**Severe:** an event that prevents normal everyday activities.

Note: the term 'severe', used to describe the intensity, should not be confused with 'serious' which is a regulatory definition based on participant/event outcome or action criteria. For example, a headache may be severe but not serious, while a minor stroke is serious but may not be severe.

### 10.5 REPORTING OF SAES/SARS/SUSARS

Once the Investigator becomes aware that an SAE has occurred in a study participant, the information will be reported to the ACCORD Research Governance & QA Office **immediately or within 24 hours**. If the Investigator does not have all information regarding an SAE, they should not wait for this additional information before notifying ACCORD. The SAE report form can be updated when the additional information is received. Elective admission for LNG-IUS insertion or elective admission for hysterectomy would not need to be classified as a serious adverse event.

The SAE report will provide an assessment of causality and expectedness at the time of the initial report to ACCORD according to sections 10.4.2, Assessment of Causality and 10.4.3, Assessment of Expectedness.

The SAE form will be transmitted by fax to ACCORD on **[name]** or submitted via email to [[contact]](mailto:[contact]). Only forms in a pdf format will be accepted by ACCORD via email.

Where missing information has not been sent to ACCORD after an initial report, ACCORD will contact the investigator and request the missing information.

All reports faxed to ACCORD and any follow up information will be retained by the Investigator in the Investigator Site File (ISF). Details received by ACCORD will be passed on to BCTU in their capacity as Coordinating Centre.

## **10.6 REGULATORY REPORTING REQUIREMENTS**

The ACCORD Research Governance & QA Office is responsible for pharmacovigilance reporting on behalf of the co-sponsors (Edinburgh University and NHS Lothian).

The ACCORD Research Governance & QA Office has a legal responsibility to notify the regulatory competent authority and relevant ethics committee (Research Ethics Committee (REC) that approved the trial). Fatal or life threatening SUSARs will be reported no later than 7 calendar days and all other SUSARs will be reported no later than 15 calendar days after ACCORD is first aware of the reaction.

ACCORD will inform Investigators at participating sites of all SUSARs and any other arising safety information.

An Annual Safety Report/Development Safety Update Report will be submitted, by ACCORD, to the regulatory authorities and RECs listing all SARs and SUSARs.

## **10.7 FOLLOW UP PROCEDURES**

After initially recording an unexpected AE or recording and reporting an SAE, the Investigator should make every effort to follow each event until a final outcome can be recorded or reported. The Investigator should follow each unexpected AE or SAE until the event has resolved, the event is assessed as stable by the Investigator, the participant is lost to follow up, or the participant withdraws consent. Follow up information on an SAE will be reported to the ACCORD office.

If, after follow up, resolution of an event cannot be established, an explanation should be recorded.

In the case of PAECs observed at 12 months in those allocated UPA, the women should be reassessed until an endometrial biopsy confirms the restoration of a normal endometrium.

## **10.8 PREGNANCY**

Pregnancy will be considered an AE if women are compliant with either trial treatment. If a woman withdraws from trial treatment and conceives within 12 months of randomisation, this **will not** be considered an AE. However, the investigator will collect pregnancy information for any female participants while participating in the study. The Investigator will record the information on a Pregnancy Notification Form and submit this to the [[contact]](mailto:[contact]) or **[name]** within 14 days of being made aware of the pregnancy. BCTU will follow-up any self-reported pregnancies with the women's GP or gynaecologist. All pregnant female participants will be followed

up until the outcome of the pregnancy is known. Details received by the UCON Trial Office will be passed on to ACCORD.

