#### **5.6.1 Change of Treatment following USM**

Following the USM, new cycles of UPA will not be initiated. In such instances, participants will be offered alternative options for treatment of their HMB. Stopping treatment or change to treatment must be documented on the UCON trial database using the Withdrawal/Change of Status Form (NOTE: the section regarding "Withdrawal from Trial" does not need to be completed if the woman is continuing in the trial). Change of treatment will also be collected as part of the questionnaires at standard assessment times.

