#### 6.4.2 Monitoring compliance

Follow-up questionnaires will ask for self-reported compliance to the allocated treatment. We may also collect data on adherence via a text message at various time points. LNG-IUS drug compliance will be participants who have had the coil fitted within 5 weeks post-randomisation.

UPA compliance will be those participants who report in the follow-up questionnaire to have taken the drug for at least 5 days per week. UPA drug compliance may also be evaluated by 'pill-counting'.

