## **6.7 SPECIAL WARNINGS AND PRECAUTIONS FOR USE FOR LEVONORGESTREL**

### **6.7.1 Fitting of the LNG-IUS**

LNG-IUS fitting should ideally be performed by an experienced gynaecologist at the second clinic appointment. If this is not possible, a prescription can be given to enable the woman to go to a

sexual health clinic or her GP, for the coil to be fitted by a clinician as per standard clinical care and current service provision.

Perforation of the uterine corpus or cervix may occur, most commonly during insertion. This may be associated with severe pain and continued bleeding. If perforation is suspected the system should be removed as soon as possible and reported as a trial treatment withdrawal to the UCON Trial Office.

The insertion tube for LNG-IUS has been designed to minimise the risk of infections. Women should be told to be aware of symptoms and signs suggestive of pelvic infection and to go to her GP if at all concerned.

The RCOG guidelines suggest a women should be re-examined six weeks after insertion and further examinations should be performed where clinically indicated, but this will be left to the discretion of the gynaecologist to advise.

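### Section 10.8 makes the adverse-event status of a pregnancy depend on compliance after randomisation, so pregnancy AE counts are not like-for-like between the arms

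*Protocol*

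**What the plan says.** Section 10.8 gives two rules on AE status and two on data collection.

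- AE status: "Pregnancy will be considered an AE if women are compliant with either trial treatment".
- AE status after stopping: the sentence that begins "If a woman withdraws from trial treatment and conceives within 12 months of randomisation, this" goes on to say that such a conception is not an AE.
- Collection: "However, the investigator will collect pregnancy information for any female participants while participating in the study". A Pregnancy Notification Form is due within 14 days of awareness.
- Follow-up: "All pregnant female participants will be followed" until the outcome is known.

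Compliance is defined only in section 6.4.2, separately by arm. For the coil: "LNG-IUS drug compliance will be participants who have had the coil fitted within 5 weeks post-randomisation". For the tablets: "UPA compliance will be those participants who report in the follow-up questionnaire to have taken the drug for at least 5 days per week".

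Section 5.6.1 (Change of Treatment following USM) adds: "Following the USM, new cycles of UPA will not be initiated". Under the Important Notice, women who stop treatment stay in the trial and are followed up.

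The general AE definition in section 10.1 covers any untoward event in a participant and does not mention compliance. Section 9.2 sets intention-to-treat analysis and data collection on all randomised women regardless of compliance.

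**The concern.** Compliance and withdrawal happen after randomisation, and here they take different forms in the two arms. A count restricted by them no longer compares the groups as randomised. Pregnancy is an event on which the arms could plausibly differ: section 6.8.2 describes the LNG-IUS as a highly effective contraceptive, whereas women on UPA who need contraception use barrier methods (6.5.2).

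Two uses of AE data are exposed. Section 2.1.2 makes adverse events reported by participants part of a between-arm secondary objective. Section 11.4 promises the Data Monitoring Committee interim analyses of the primary outcome and adverse events. Pregnancy is not a listed outcome in 2.2.2 and has no analysis in 9.2.2, so the AE label governs what is shown by default.

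**Working it through.** The protocol gives no pregnancy, expulsion or non-compliance rate, so there is no figure of its own to reproduce. The check is to apply 10.8, with the definitions in 6.4.2, to the situations that the protocol foresees.

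| Situation at conception | Status | AE under 10.8? |
|---|---|---|
| UPA on 4 days a week | Below the 5-day threshold: not compliant | No, although drug-exposed |
| UPA on 5 or 6 days a week | Compliant | Yes |
| UPA, planned 4-week break | Not addressed | Unclear |
| UPA not restarted after the safety measure | Withdrawn, or below 5 days a week | No, on either description |
| Coil fitted within 5 weeks, in place | Compliant | Yes |
| Coil fitted within 5 weeks, expelled unnoticed (possibility raised in 6.8.2) | Still compliant: no retention requirement | Yes |
| Coil fitted after 5 weeks, in place (6.2.2 allows later fitting) | Not compliant | No |
| Coil removed for suspected perforation (6.7.1) | "removed as soon as possible and reported as a trial treatment withdrawal to the UCON Trial Office" | No |

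Two things follow. First, the conditions differ in kind: one fitting date against continuing intake. Secondly, pregnancies lose AE status in both arms, by different routes.

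To see what this does to counts, write the reported AE count in an arm as N × (1 − f). N is the number of pregnancies and f the share that loses AE status. All values below are assumptions.

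- Equal true counts, N = 4 per arm, no LNG-IUS pregnancy excluded, f in UPA of 25%, 50% or 75%: UPA reports 4 × 0.75 = 3, 4 × 0.50 = 2 or 4 × 0.25 = 1, against 4 for LNG-IUS.
- The same with N = 2: an expected 1.5, 1 or 0.5 against 2. With N = 6: 4.5, 3 or 1.5 against 6.
- The exclusions placed in the LNG-IUS arm instead, N = 4: 4 for UPA against 3, 2 or 1.
- Equal f in both arms: equal reported counts.
- Unequal true counts, 4 v 1, with 220/2 = 110 women per arm: 4/110 = 3.6% v 1/110 = 0.9%. If 3 of the 4 UPA pregnancies lose AE status and the LNG-IUS one does not, the AE counts are 1 v 1.

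The AE counts can thus show a difference where there is none, or mask one that exists. Which of these happens depends on the two values of f, and the protocol gives neither.

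**The case against.** The strongest reply is that no pregnancy is hidden. Section 10.8 requires a form for any participant who conceives and follow-up to outcome, and the follow-up questionnaires ask both arms about pregnancies (8.1.1). This stands: the loss is in the AE label, not in the data, and a comparison by allocated arm remains possible among women still in follow-up.

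Next, 10.8 does not cite 6.4.2, so joining them is an inference. UPA compliance is read from questionnaires at about 3, 6 and 12 months, whereas a pregnancy form is due within 14 days; 6.4.2 may be meant for adherence monitoring only. That is fair, but the protocol has no other definition. If 6.4.2 does not apply, compliance in 10.8 is undefined, which also needs correcting.

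Thirdly, the listed safety outcome in 2.2.2 is serious adverse events and reactions, and no section compares pregnancies by AE label. This limits the consequence to the two uses of AE data named above, and the committee can request further analyses.

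Fourthly, the withdrawal rule has a rationale: a wish to conceive is a reason for stopping treatment (5.6.5), and a planned conception is not untoward. This stands for planned conceptions. It does not cover a woman whose treatment was ended by the safety measure.

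A reader might infer more: that the rule conceals UPA pregnancies while keeping those after a lost coil, or reverses the comparison. The documents do not support this. The withdrawal sentence covers both arms, late fitting and removal take pregnancies out of the LNG-IUS count, tablets missed on up to two days a week still count as compliant, and the 4 v 1 example is assumed and shows masking only.

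**Conclusion.** The point holds as a matter of classification. Section 10.8 filters one type of event by post-randomisation behaviour, without a definition of its own and against 10.1 and the intention-to-treat principle in 9.2. After the safety measure the filter also acts unequally, because women whose UPA treatment was still running come off drug while coils can stay in place. Pregnancy AE counts are not like-for-like by arm.

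Direction and size cannot be determined from the protocol. The detailed contrasts assume that 6.4.2 supplies the meaning of compliance; the undefined term and the departure from 10.1 do not depend on that. The primary MMAS analysis is unaffected: the allowance for pregnancy in 9.1.1 concerns loss of outcome data, which does not depend on the AE label. Severity is minor.

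**What to change.** - In 10.8 and 9.2.2, state that all pregnancies up to 12 months after randomisation will be tabulated by allocated arm, from the Pregnancy Notification Forms and questionnaires already collected, with the number randomised and the number still in follow-up.
- Show treatment status at conception (on UPA, between courses, stopped, coil in place, expelled, removed or never fitted) as description, not as a condition for counting. Mark planned conceptions after stopping treatment with a footnote.
- Give the same table to the Data Monitoring Committee with the AE report.
- Reconcile 10.8 with 6.4.2 and 10.1: either say what compliance means for this purpose, including after the safety measure, or remove the condition. The table does not depend on which is chosen.

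The cost is a few sentences and one small table, with no new forms. The downside is that planned pregnancies after withdrawal will appear in the table, hence the footnote.

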## **11 TRIAL MANAGEMENT AND OVERSIGHT ARRANGEMENTS**

### **11.1 TRIAL MANAGEMENT GROUP**

The trial will be coordinated by a Trial Management Group (TMG), consisting of the Chief Investigator, all other grant holders, the Trial Manager and Edinburgh based research nurse. The TMG will meet regularly, by teleconference or face to face.

### **11.2 THE UCON TRIAL OFFICE**

The Trial Office at Birmingham Clinical Trials Unit (BCTU), University of Birmingham is responsible for the day to day management of the UCON Trial. The Trial Manager, based at BCTU, will oversee the study and will be accountable to the Chief Investigator. The Data Manager will be responsible for checking the data forms for completeness, plausibility and consistency. Any queries will be resolved by the Investigator or delegated member of the trial team.

The UCON Trial Office will also be responsible for providing all trial materials, including an Investigator Site File (ISF), with copies of all essential documents, and a trial stationary folders containing all required printed materials e.g. participant information sheets, consent forms. These will be supplied to each collaborating centre, after relevant local research governance approval has been obtained. Additional supplies of any printed material can be obtained on request. The Trial Office also provides the central randomisation service and is responsible for collection and checking of data (including reports of serious adverse events thought to be due to trial treatment), The Trial Office will help resolve any local problems that may be encountered in trial participation.

### **11.3 TRIAL STEERING COMMITTEE**

A Trial Steering Committee (TSC) will be established to oversee the conduct and progress of the trial. Names and contact details are given on page iv.

The Trial Steering Committee (TSC) provides independent supervision for the trial, providing advice to the Chief and Co- Investigators and the Sponsor on all aspects of the trial and affording protection for patients by ensuring the trial is conducted according to the International Committee on Harmonisation Guidelines for Good Clinical Practice in Clinical Trials.

If the Chief and Co-Investigators are unable to resolve any concern satisfactorily, Principal Investigators, and all others associated with the study, may write through the Trial Office to the chairman of the TSC, drawing attention to any concerns they may have about the possibility of particular side-effects, or of particular categories of patient requiring special study, or about any other matters thought relevant.

The Trial office will forward TSC meeting minutes to the Sponsor and funder. Terms of reference of the Trial Steering Committee and the draft template for reporting will be agreed at the inaugural meeting.

#### **11.4 DATA MONITORING COMMITTEE**

An independent Data Monitoring Committee (DMC) will be established to oversee the safety of participants in the trial. Names and contact details are given on page iv.

If one treatment really is substantially better or worse than any other with respect to the primary outcome, then this may become apparent before the target recruitment has been reached. Alternatively, new evidence might emerge from other sources that any one treatment is definitely more, or less, effective than any other. To protect against this, during the main period of recruitment to the study, interim analyses of the primary outcome and adverse events will be supplied, in strict confidence, to the independent DMC, along with updates on results of other related studies, and any other analyses that the DMC may request. The DMC will advise the chair of the TSC if, in their view, any of the randomised comparisons in the trial have provided both (a) “proof beyond reasonable doubt” that for all, or for some, types of patient one particular treatment is definitely indicated or definitely contraindicated in terms of a net difference in the major endpoints, and (b) evidence that might reasonably be expected to influence the patient management of many clinicians who are already aware of the other main trial results. The TSC can then decide whether to close or modify any part of the trial. Unless this happens, however, the TMG, TSC, the investigators and all of the central administrative staff (except the statisticians who supply the confidential analyses) will remain unaware of the interim results.

The BCTU Trial office will forward DMC open meeting minutes to the Sponsor and funder. Terms of reference of the Trial Steering Committee and the draft template for reporting will be agreed at the inaugural meeting.

#### **11.5 INSPECTION OF RECORDS**

Investigators and institutions involved in the study will permit trial related monitoring and audits on behalf of the sponsor, REC review, and regulatory inspection(s). In the event of an audit or monitoring, the Investigator agrees to allow the representatives of the sponsor direct access to all study records and source documentation. In the event of regulatory inspection, the Investigator agrees to allow inspectors direct access to all study records and source documentation.

#### **11.6 RISK ASSESSMENT**

An independent risk assessment will be performed by an ACCORD Clinical Trials Monitor to determine if monitoring is required and if so, at what level. An independent risk assessment will also be carried out by the ACCORD Quality Assurance Group to determine if an audit should be performed before, during or after the study and if so, at what locations and at what frequency.

---

 Appropriate criteria of proof beyond reasonable doubt cannot be specified precisely, but a difference of at least  $p < 0.001$  (similar to a Haybittle-Peto stopping boundary) in an interim analysis of a major endpoint may be needed to justify halting, or modifying, the study prematurely. If this criterion were to be adopted, it would have the practical advantage that the exact number of interim analyses would be of little importance, so no fixed schedule is proposed.

## **11.7 STUDY MONITORING AND AUDIT**

An ACCORD Clinical Trials Monitor or an appointed monitor may visit the Investigator site prior to the start of the study and/or during the course of the study if required, in accordance with the central monitoring plan.

Investigators and their host Trusts will be required to permit trial-related monitoring and audits to take place by either the ACCORD Clinical Trials Monitor and/or Trial Coordinator as and when required who would require direct access to source data and documents as requested. Risk assessment will determine if audit, by the ACCORD QA group, is required. Details will be captured in an audit plan. Audit of Investigator sites, study management activities and study collaborative units, facilities and 3rd parties may be performed.

The study will also adopt a centralised approach to monitoring data quality and compliance. A computer database will be constructed specifically for the trial data and will include range and logic checks to prevent erroneous data entry. Independent checking of data entry will be periodically undertaken on small sub-samples. The trial statistician will regularly check the balance of allocations by the stratification variables.

Trusts may also be subject to inspection by the Medicines and Healthcare Products Regulatory Agency and/ or by the Research and Development Manager of their own Trust and should do everything requested by the Chief Investigator in order to prepare and contribute to any inspection or audit. Trial participants will be made aware of the possibility of external audit of data they provide in the participant information sheet.

